### 2.6. Primary Outcome

The primary outcome is the modified Rankin Scale (mRS) score at 90 days post-stroke. The mRS ranges from 0 (no symptoms) to 6 (death) and is the most widely used functional outcome measure in stroke trials [25]. An mRS ≤ 2 at 90 days is defined as a favorable outcome (Table 2).

### 2.7. Secondary Outcomes

As secondary outcomes, we first selected the item of change in muscle atrophy using ultrasound examination [7,22]. This will allow us to determine the optimal MQS dose for muscle atrophy results. Next, we selected the items of the Barthel Index [26], Medical Research Council score [27], functional status score in ICU [28], grip strength [29], Clinical Frailty Scale [30], return to work, and complications. We aim to investigate these items and quantify ICU-acquired weakness from multiple perspectives (Table 2). We will also record adverse events during the rehabilitation intervention (falls, cardiac arrest, tachycardia > 130 bpm, systolic blood pressure < 80 or >200, ventricular tachycardia, other dangerous arrhythmias, arterial oxygen saturation of pulse oximetry < 80% for >3 min, and other device removal).

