## 1. Introduction

Stroke is a leading cause of disability worldwide [1] and ranks fourth among the top ten causes of death in Japan. Although advances in medical science have improved survival rates for patients with severe stroke in recent years, the number of individuals living with long-term physical and cognitive sequelae has increased [2,3]. Among these, muscle atrophy in the paralyzed limbs of patients with hemiplegia, referred to as central atrophy, significantly affects both functional independence and quality of life [4]. In addition to stroke-related disability, critically ill patients may experience other complications, such as intensive care unit (ICU) acquired weakness, characterized by generalized weakness of the limbs and respiratory muscles, further impeding recovery [5,6]. Skeletal muscle atrophy in severely ill patients progresses rapidly by approximately 2% per day, amounting to a 12% reduction in muscle mass per week, and is directly associated with loss of functional independence and reduced quality of life. Therefore, early detection and prevention of muscle atrophy are crucial [7].

Rehabilitation is a primary strategy to promote functional recovery and enhance independence in stroke patients [8]. Once the patient’s neurological symptoms and vital signs stabilize during the acute phase, those with functional impairments transition to the post-acute phase and begin rehabilitation. Traditionally, active rehabilitation has been implemented during the post-acute phase, when patients are medically stable, with the goal of minimizing long-term disability [9]. More recently, increasing attention has been paid to early mobilization in critically ill patients. While several studies have reported the safety of early mobilization, its effectiveness remains a subject of debate [10]. Several systematic reviews and guideline papers have highlighted both the potential benefits and uncertainties of very early mobilization after stroke, noting variability in outcomes depending on patient severity, timing, and dose of interventions [11,12,13]. For example, one study reported that very early mobilization was associated with poorer functional outcomes and higher rates of adverse events at 3 months post-stroke compared to standard care [14]. However, a post hoc analysis of the same cohort revealed that patients who received shorter and more frequent mobilization sessions had significantly improved functional outcomes [15].

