Despite growing interest in early mobilization after stroke, key uncertainties remain. First, the optimal dose and timing in the acute phase are unresolved, with heterogeneous and sometimes conflicting results [14,15,20]. Second, most studies lack a standardized, quantitative dose metric, limiting cross-study comparability; the Mobilization Quantification Score (MQS) addresses this by integrating mobilization level and duration [16,21]. Finally, early-phase studies rarely incorporate objective muscle-atrophy assessments (e.g., rectus femoris ultrasound) despite prognostic relevance [7,22]. We hypothesize that the optimal rehabilitation dose during the acute phase of stroke varies by stroke severity: higher-intensity mobilization may promote greater independence in activities of daily living at 90 days post-stroke in patients with mild strokes, whereas lower-intensity mobilization may be more beneficial in those with severe strokes. We hypothesize that a higher early rehabilitation dose will be associated with better functional outcomes at 90 days. We further hypothesize that baseline stroke severity modifies this association: patients with mild-to-moderate stroke will benefit from higher MQS [21], whereas patients with severe stroke may benefit from moderate doses. Secondary hypotheses are that higher MQS will be associated with less rectus femoris muscle atrophy on ultrasound and better performance on physical assessment. To test this hypothesis, we will use the MQS to assess rehabilitation dose. In addition, we will analyze patient background characteristics, nutritional status, muscle atrophy, and differences in rehabilitation protocols across participating facilities. This study aims to establish standardized and optimized early mobilization practices and to evaluate the relationship between MQS-based rehabilitation dosage and functional independence in stroke patients.

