### 2.9. Data Source/Measurements

At each of the above time points, ultrasound will be used to evaluate the cross-sectional area and muscle thickness of the rectus femoris. All collected data will be prepared according to standard protocols published in the field and analyzed by a team experienced in muscle ultrasound (physiotherapists and/or neurologists and rehabilitation physicians currently working in the hospital).

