### 2.14. Statistical Methods

There is no maximum sample size for this study; however, the outcome may be subject to targets or maximum sample sizes, which will be specified in the relevant sub-protocol. The expected sample size is ≥200 patients (minimum 10 patients/facilities, ≥20 facilities) to provide a sufficient number of different rehabilitation doses to predict functional outcomes and build robust models for protocol use. To avoid over-representation of some centers, data collection is limited to 50 patients per facility. Patient enrollment will therefore not be strictly equal across hospitals; each facility is expected to enroll at least 10 patients, with a maximum of 50 patients, depending on their clinical volume. This strategy ensures diversity in practice patterns while preventing over-representation of any single center. The number of enrolled patients and facilities is a sufficient sample size to capture the various variations in practice and treatment. It is considered feasible to collect a sample of this calculated size because each participating facility should be able to enroll at least one patient per month based on the number of stroke patients hospitalized at each facility in the past.

Baseline characteristics and outcomes will be summarized using descriptive statistics. Continuous variables will be presented as means with standard deviations (SDs) or medians with interquartile ranges (IQRs), while categorical variables will be presented as frequencies and percentages (*n*, %).

The primary analysis will examine the association between the mean rehabilitation dose (MQS score) during the first 7 days of hospitalization and the primary outcome of a favorable functional outcome (mRS ≤ 2) at 90 days. This association will be evaluated using a multivariable logistic regression model. The model will be adjusted for a pre-specified set of covariates selected for their established prognostic significance, including age, sex, pre-admission mRS, baseline National Institutes of Health Stroke Scale (NIHSS) score, stroke subtype (ischemic or hemorrhagic), and participating facility (as a random effect).

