For secondary outcomes, multivariable linear regression models will be used for continuous variables, such as the Barthel Index. A pre-specified subgroup analysis will be conducted to explore whether the effect of rehabilitation dose is modified by initial stroke severity. An interaction term between the MQS score and the severity category (defined by baseline NIHSS) will be introduced into the primary model.

Time-to-event outcomes will be analyzed using Kaplan–Meier curves and Cox proportional hazards regression models, adjusted for baseline characteristics. For survival analysis, patients will be stratified into groups based on quartiles of rehabilitation volume and pre-defined stroke severity categories. Missing data for covariates will be handled using multiple imputation under the missing-at-random assumption. The primary analysis will be based on the pooled results from the imputed datasets, with a complete-case analysis performed as a sensitivity analysis.

All statistical analyses will be performed using JMP (version 13.0; SAS Institute, Cary, NC, USA) and IBM SPSS software (version 23.0; IBM, Armonk, NY, USA). A two-sided *p*-value of <0.05 will be considered statistically significant.

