**ASSESSMENTS:**				
Baseline variables	×			
Muscle cross-sectional area muscle thickness	×	×		
Physical functions (Clinical Frail Scale)	×	×	×	×
Physical functions (Functional status score-ICU, Barthel index)		×	×	
Muscle strength (Medical Research Council, Handgrip)		×	×	
mRS	×	×	×	×
Exposure ascertainment (MQS; mean of Days 1–7)		×	×	

Abbreviations: ICU; intensive care unit, mRS; modified Rankin Scale, MQS; Mobilization Quantification Score.

**Table 2 jcm-14-06786-t002:** Details of outcome measures at follow-up.

Variable	Description
Survival	If a patient dies during follow-up, date of death is recorded
Employment status	Whether the patient/family has a job at follow-up (full-time or part-time) and whether the job is the same as before hospital admission
General information	Readmission to hospital during follow-up
National Institutes of Health Stroke Scale	The National Institutes of Health Stroke Scale is a 15-item impairment scale, intended to evaluate neurologic outcome and degree of recovery for patients with stroke. The scale assesses level of consciousness, extraocular movements, visual fields, facial muscle function, extremity strength, sensory function, coordination, language, speech, and hemi-inattention.
Physical function/activities of daily living	
mRS	The mRS ranges from 0 (no symptoms) to 6 (death) and is the most widely used functional outcome measure in stroke trials. An mRS ≤ 2 at 90 days is defined as a favorable outcome.
Clinical Frail Scale	The Clinical Frailty Scale is a judgment-based frailty tool that evaluates specific domains, including comorbidity, function, and cognition, to generate a frailty score ranging from 1 (very fit) to 9 (terminally ill).
FSS-ICU	The FSS-ICU is a performance-based measure that assesses physical function in critically ill patients. It evaluates five tasks: (1) rolling, (2) supine to sit transfer, (3) sitting at the edge of the bed, (4) sit to stand transfer, and (5) walking. Each task is scored from 0 (unable to perform) to 7 (complete independence), for a total score ranging from 0 to 35. Higher scores indicate better physical function.

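### The muscle-change outcome has no stated scale and no covariate list that names the admission muscle size measured at T0; adding it would guard against a bias that could run in either direction

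*Protocol article*

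**What the plan says.** Protocol article, section 2.7, opens the secondary outcomes with muscle: "we first selected the item of change in muscle atrophy using ultrasound examination". It adds that this outcome is meant to identify the best MQS dose for muscle. The Introduction gives it a direction: "Secondary hypotheses are that higher MQS will be associated with less rectus femoris muscle atrophy on ultrasound".

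Section 2.14 covers it only generically: "multivariable linear regression models will be used for continuous variables, such as the Barthel Index". No covariates are attached to the secondary models. The one covariate list belongs to the primary mRS model, "including age, sex, pre-admission mRS, baseline National Institutes of Health Stroke Scale (NIHSS) score, stroke subtype (ischemic or hemorrhagic), and participating facility", and contains no muscle measure. The Discussion describes wider control for comorbidity, nutrition, rehabilitation policy and staffing, again without muscle size.

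In Table 1 the row "Muscle cross-sectional area muscle thickness" carries two marks, which read as T0 (admission) and T1 (day 7). Section 2.9 is broader: "At each of the above time points, ultrasound will be used to evaluate the cross-sectional area". Admission is measured on either reading.

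The only expected rate of loss is proportional and is given for severely ill patients: it "progresses rapidly by approximately 2% per day, amounting to a 12% reduction in muscle mass per week".

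**The concern.** A change score is not automatically free of starting size. If everyone loses 12%, a 5 cm² muscle loses 0.60 cm² and a 3 cm² muscle loses 0.36 cm². If instead everyone loses about the same area, the percentage loss is larger in the smaller muscle. In either case, a change measured on the mismatched scale depends on admission size.

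Usual care sets the dose here, so MQS may be related to admission size through frailty, nutrition or body build. Those are recorded under section 2.8 but are not in the primary-model list. Any such relation left after adjustment would enter the MQS coefficient. At stake is the size, and possibly the sign, of the answer to a directional secondary hypothesis. An open scale also leaves absolute or percentage change to be chosen once the data are known.

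**Working it through.** **The plan's own figure.** Section 2.14 expects at least 200 patients: 10 per facility × 20 facilities = 200. No effect, SD or power is given for muscle, so there is nothing further to reproduce. The simulation uses n = 200 and two-sided 0.05.

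**Inputs from the article.** Weekly loss of 12% (Introduction). Measurement error of 3%, the upper limit in section 2.10.

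**Assumed inputs.** CV of admission size 20–30%. Residual SD of loss 5 points. Correlation r between the parts of MQS and admission size not explained by an age/sex composite, from −0.3 to +0.5. True benefit 1.0 point (1% of mean admission size) less loss per SD of MQS. The composite correlates 0.5 with size and 0.3 with MQS.

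**Large-sample formula** for absolute change, proportional loss and no admission size in the model:

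bias = −(loss in points) × CV × (slope of standardised size on MQS, given the composite), where that slope = r × √(1 − 0.25)/√(1 − 0.09) = 0.908r.

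- r = +0.3, CV 20%: −12 × 0.20 × 0.908 × 0.3 = −0.65, so 1.0 becomes 0.35.
- r = +0.3, CV 30%: −12 × 0.30 × 0.908 × 0.3 = −0.98, so 0.02.
- r = +0.5, CV 25%: −12 × 0.25 × 0.908 × 0.5 = −1.36, so −0.36.
- r = −0.3, CV 25%: +0.82, so 1.82.

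**Simulation** (1,500 runs per cell). Mean MQS slope when the truth is 1.0; CV 25% unless two values are shown, which are for CV 20% and 30%. Ranges cover every r and CV run in that row.

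| Change scale | Loss | r | Without admission size | With admission size |
|---|---|---|---|---|
| Absolute | proportional | −0.3 | 1.83 | 0.85 |
| Absolute | proportional | 0 | 1.02 | 1.01 |
| Absolute | proportional | +0.3 | 0.35; 0.03 | 1.16; 1.12 |
| Absolute | proportional | +0.5 | −0.37 | 1.25 |
| Percentage | proportional | −0.3 to +0.5 | 0.97 to 1.00 | 0.87 to 1.26 |
| Absolute | not proportional | −0.3 to +0.5 | 0.98 to 1.02 | 0.84 to 1.30 |
| Percentage | not proportional | −0.3 | 0.04 | 0.91 |
| Percentage | not proportional | 0 | 1.09 | 1.06 |
| Percentage | not proportional | +0.3 | 1.84; 2.57 | 1.22; 1.27 |
| Percentage | not proportional | +0.5 | 2.86 | 1.40 |

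In the third row, power falls from 64% and 59% with admission size to 9% and 4% without it.

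**No true effect, r = +0.3, CV 20% and 30%.** Absolute change with proportional loss wrongly shows more loss at higher dose in 24% and 44% of studies. Percentage change with non-proportional loss wrongly shows a benefit in 30% and 56%. With admission size in the model, total rejection is 5% to 7% in all four combinations of scale and loss.

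**Sensitivity to the loss fraction.** The formula is linear in loss. At an assumed 6%, the r = +0.3 bias halves to −0.33 (CV 20%) and −0.49 (CV 30%), leaving 0.67 and 0.51 of a true 1.0.

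**Algebra.** With admission size as a covariate, regressing absolute change or day-7 size gives the identical MQS coefficient, because the two outcomes differ only by a term already in the model. The same holds for the log ratio and log day-7 size, given log admission size.

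**The case against.** A reader might infer that the plan models muscle change without admission size, that high-dose patients have larger muscles, and that a real benefit will therefore be hidden. The documents do not support this.

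- **Omission is inferred from silence.** The article names no covariates for any secondary model and is a condensed text; a fuller analysis plan may include admission size. This stands.
- **Absolute change is not specified.** The article's atrophy figures are percentages, so percentage change is at least as natural a reading. With proportional loss it needs no baseline term. This stands, and it is why the scale has to be stated.
- **The correlation is unknown.** Nothing in the article says that MQS rises with muscle size. At r = 0 there is no masking, and at a negative r absolute change would overstate the benefit. This stands. Sign reversal on the absolute scale appeared only at r = +0.5.
- **The 12% rate is for severely ill patients.** This cohort includes milder stroke, so the bias may be smaller. This stands.
- **Adjustment is not bias-free in a cohort.** The adjusted slopes are not exactly 1.0. With no true effect and r = +0.3 they averaged 0.11 to 0.17, mainly because the 3% error in the admission scan is shared with the change score. Such error would not by itself bias an unadjusted slope when dose does not depend on it. This stands as a caveat.

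The objection does not remove the case for the baseline term. Across the table the unadjusted slope runs from −0.37 to 2.86 and the adjusted slope from 0.84 to 1.40. Without admission size, the answer depends on an unstated scale and an unknown correlation.

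**Conclusion.** The point holds as a low-cost improvement, not as a demonstrated error. The article leaves the scale of change open and names admission muscle size in no covariate list, although the scan is scheduled.

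The possible bias is conditional. Absolute change with proportional loss understates a benefit when the residual correlation is positive and overstates it when negative. Percentage change with non-proportional loss does the opposite. Matching the scale to the loss mechanism, or zero correlation, leaves little or none. At r = +0.3 and 12% loss, between 65% and 97% of a 1.0-point benefit disappears in the first case (1 − 0.35 and 1 − 0.03). In the second case the estimate is 1.84 to 2.57 times the truth. These sizes rest on the assumed correlation, CV and loss fraction, none of which the article fixes for this cohort.

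**What to change.** In sections 2.7 and 2.14, define the muscle outcome as day-7 rectus femoris area and day-7 thickness, preferably on the log scale. Analyse each by linear regression on MQS, with the admission value (on the same scale) as a covariate beside the primary-model covariates. Report the MQS effect as a percent difference in day-7 muscle, 100 × (exp(coefficient) − 1) per unit of dose. Add a sentence acknowledging that measurement error in the admission scan leaves a small residual bias. While editing, reconcile the ultrasound time points in section 2.9 with Table 1, so that day 7 is clearly the follow-up scan.

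The cost is wording and one extra coefficient per model. No new measurement is needed, and enrolment is not due to start until June 2026. If a fuller analysis plan already says this, a cross-reference is enough.

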### 2.8. Baseline Characteristics and Treatment

The baseline characteristics of enrolled patients will be prospectively collected, including baseline factors such as age, height, weight, handedness, employment status, existing comorbidities, pre-admission mRS, and frailty; disease factors such as culprit vessel, lesion, and national institutes of health stroke scale [31]; biochemical data such as C-reactive protein, lymphocyte count, and serum albumin; and nutrition factors such as the Malnutrition Universal Screening Tool [32] at admission. The National Institutes of Health Stroke Scale will be recorded at admission, day 7, and at discharge. Details of treatments that may affect outcomes, such as surgery, use of Tissue Plasminogen Activator, noninvasive ventilation, mechanical ventilation, and tracheostomy, will also be prospectively collected.

### 2.9. Data Source/Measurements

At each of the above time points, ultrasound will be used to evaluate the cross-sectional area and muscle thickness of the rectus femoris. All collected data will be prepared according to standard protocols published in the field and analyzed by a team experienced in muscle ultrasound (physiotherapists and/or neurologists and rehabilitation physicians currently working in the hospital).

### 2.10. Ultrasonography Assessment

Ultrasound will be used to measure the rectus femoris muscle cross-sectional area and thickness in supine patients with extended knees. Measurements will be taken at the anterior superior iliac spine and the distal third of the thigh using B-mode with a linear probe. For consistency, anatomical landmarks will be marked for repeated measures. If one image cannot capture the entire muscle, it will be reconstructed from multiple sections. Each measurement is taken three times, and the median value is used. Pre-study training ensures that intra- and inter-rater variation remains below 3%.

### 2.11. Rehabilitation Protocol

Participants in the BRIDGE cohort will receive their usual rehabilitation at their respective institutions. We aim to exercise all participants equally every day, based on a five-stage protocol (Level 1: passive range of motion and respiratory physiotherapy, Level 2: active range of motion, Level 3: sitting exercise, Level 4: standing exercise, Level 5: walking exercise) tailored to each participating hospital. In addition, adverse events during implementation will also be indicated with appropriate values in the categories of medical, cardiovascular, respiratory, and neurological problems. In case of deviation from these values, the patient will be immediately placed on bed rest, and the event will be considered an adverse event. After level 5 is achieved, a physiotherapist or occupational therapist will provide each patient with rehabilitation, including muscle strengthening, balance, walking, and stair climbing, for at least 20 min on weekdays, according to the rehabilitation policy of each hospital.

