### 2.13. Rehabilitation Dose

Rehabilitation dose is defined using the MQS over days 1–7 post-admission. MQS combines mobilization level (assessed using the ICU mobility scale [33]) and duration (measured with a stopwatch). Only active mobilization time is included; preparation or rest is excluded. The MQS is averaged across the first 7 days to reflect the daily rehabilitation dose (Japanese version MQS [21]. It should be noted that rehabilitation itself continues beyond the first 7 days until hospital discharge, according to each institution’s standard practice. After discharge, patients typically continue rehabilitation in post-acute care facilities or outpatient/community settings, depending on their medical condition and regional healthcare resources. Functional outcomes at 90 days will therefore reflect the combined effect of early inpatient rehabilitation and subsequent standard care.

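### An adverse event in days 1–7 can lower the patient's own 7-day mean MQS, biasing the primary association toward the study's hypothesis by an amount the protocol does not allow one to fix

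*Protocol article*

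**What the plan says.** Four parts of the protocol article bear on this.

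- Section 2.11 (Rehabilitation Protocol): on deviation from set medical, cardiovascular, respiratory or neurological values, "the patient will be immediately placed on bed rest, and the event will be considered an adverse event". It does not say how long the rest lasts.
- Section 2.13 (Rehabilitation Dose): "Rehabilitation dose is defined using the MQS over days 1–7 post-admission". Also, "Only active mobilization time is included; preparation or rest is excluded", and "The MQS is averaged across the first 7 days to reflect the daily rehabilitation dose". Table 1 repeats the mean over days 1–7.
- Section 2.14 (Statistical Methods): "The primary analysis will examine the association between the mean rehabilitation dose (MQS score) during the first 7 days of hospitalization" and mRS ≤ 2 at 90 days. The model is a logistic regression with age, sex, pre-admission mRS, baseline NIHSS, stroke subtype and a random facility effect.
- Section 2.7 (Secondary Outcomes): "We will also record adverse events during the rehabilitation intervention". Nothing links these events to the exposure or to the primary model.

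The Introduction states the expected direction: "We hypothesize that a higher early rehabilitation dose will be associated with better functional outcomes at 90 days".

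**The concern.** The exposure is measured over a week in which the patient's course can change the exposure itself. A patient who breaches a limit on day 3 is put to bed. Bed rest adds no active time, but those days stay in the average. The same event may make a good 90-day mRS less likely. Patients with events therefore move toward the low-dose end and toward poor outcome together.

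Every adjustment variable apart from facility is fixed at or before admission, so none can account for something that happens later. Adding the event as a covariate would not solve this. Where dose does influence events, that would adjust for a mediator.

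The bias favours the study's own hypothesis. The Discussion promises severity-specific dose targets and input to guidelines, and the severity interaction uses the same exposure. If event rates differ by severity, which the protocol does not say, the bias would differ between strata too.

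**Working it through.** The protocol gives no event rate, length of bed rest, MQS distribution, effect size or power, so there is no stated figure to reproduce. The check has three steps.

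**1. Arithmetic of the mean.** Take a patient with a constant intended daily dose and an event on day 3, losing half that day's session plus *r* later days. The share of the intended 7-day mean that remains is (7 − 0.5 − r)/7.

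- Session only, r = 0: 6.5/7 = 93%
- One day, r = 1: 5.5/7 = 79%
- Two days, r = 2: 4.5/7 = 64%
- To day 7, r = 4: 2.5/7 = 36%

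**2. Effect on the odds ratio.** Simulation with 600,000 patients per scenario. All inputs are assumptions; none comes from the protocol. Intended dose is log-normal (SD of log dose 0.4 unless stated) and falls with NIHSS. Event odds rise 1.5-fold per SD of log dose. The event alone lowers the odds of mRS ≤ 2, by the harm factor shown, and dose has no other effect. Event day is uniform over days 1–7. The logistic model adjusts for NIHSS. Entries are ORs per SD of the exposure; *intended* is the dose the patient would have received without the event.

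| Events | Harm factor | Intended | Session only | 1 day | 2 days | 3 days | To day 7 |
|---|---|---|---|---|---|---|---|
| 6% | 3 | 0.977 | 0.988 | 1.010 | 1.029 | 1.043 | 1.066 |
| 11% | 1.5 | 0.984 | 0.992 | 1.006 | 1.018 | 1.028 | 1.041 |
| 11% | 3 | 0.956 | 0.977 | 1.016 | 1.051 | 1.078 | 1.118 |
| 21% | 3 | 0.928 | 0.962 | 1.027 | 1.089 | 1.138 | 1.201 |

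The planned mean moves toward apparent benefit in every row. With session-only loss it never crosses 1. With SD of log dose 0.8 (11% events, factor 3), the intended dose gives 0.961 and the planned mean gives 0.971 (session only), 0.988 (1 day), 1.017 (3 days) and 1.038 (to day 7). Crossing 1 is not automatic even at SD 0.4: with event odds doubling per SD and about 22% events, one rest day gives 0.975 against 0.871.

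A weaker dependence of events on dose (OR 1.3 per SD, about 11% events, log-odds harm 1.0) gives about 0.97 for the truth, 0.99 for session only, 1.02 with one day and 1.05 with two.

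**3. Does dose have to cause the events, and can the bias be removed?** A second simulation (200,000 patients per scenario) let dose rise over the week, with a strong case of 25% events, five rest days and log-odds harm 1.5.

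| Event OR per SD | Truth | 7-day mean | Pre-event mean, unstandardized | Pre-event mean, day-standardized |
|---|---|---|---|---|
| 1.0 | 1.00 | 1.31 | 1.18 | 1.00 |
| 1.3 | 0.93 | 1.30 | 1.15 | 0.95 |

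The bias is present when events have nothing to do with dose. Cutting the exposure at the event without standardizing leaves much of it, because early days carry less dose. Standardizing by hospital day recovers the truth closely.

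**The case against.** **Length of rest.** Section 2.11 concerns events during a session, and several of those listed in section 2.7 can be brief, such as tachycardia or low saturation. Stopping the session is a natural reading, and step 2 then shows dilution, not reversal. This stands: reversal is conditional on something the protocol does not state.

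**Size against precision.** With 200 patients and an assumed 50% favourable rate, the SE of the log-OR per SD is about 1/√(200 × 0.25) = 0.14. The shift from 0.97 to 1.05 is ln(1.05/0.97) = 0.08, a little over half an SE. Section 2.14 also seeks a variety of doses, and wide spread shrinks the bias. Both points limit the size; neither removes the direction, and the bias does not shrink as enrolment grows.

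**Generic limitation.** The Discussion concedes that causality cannot be established, and section 2.14 claims only an association. Neither names this feedback, whose direction can be known in advance.

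**Condensed article.** Event-date fields and sensitivity analyses may sit in the full protocol or analysis plan. That is fair for missing detail, but the exposure definition and primary model are fixed here.

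**A stronger reading.** A reader might infer that harm caused by high dose will be analysed as the result of low dose, and that the sign will reverse. One could picture a patient at MQS 20 on days 1–2 and at rest afterwards, whose mean is (20 + 20 + 0 × 5)/7 = 5.7. The documents do not support this. Five rest days and 25% events are assumptions at the strong end. Step 3 shows that dose-caused harm is not needed for the bias. The trial cited in the Introduction is reported as an association at 3 months, not as events in first-week sessions. Falls are in the recording list of section 2.7, but the bed-rest rule concerns set limits.

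**Conclusion.** The concern holds in conditional form. Sections 2.11, 2.13 and 2.14 together allow an event in days 1–7 to reduce the patient's own exposure value while it may also worsen the outcome. The result is reverse causation toward the study's hypothesis, which the listed covariates cannot remove. It also arises if dose plays no part in causing the events.

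The size cannot be settled from the protocol. Under moderate assumed inputs, a true OR of about 0.97 per SD is read as 0.99 to 1.05, depending on whether rest lasts for the session, one day or two. Larger reversals need frequent events and long rest, and wide dose spread reduces the shift. These figures show direction and range; they are not predictions for this cohort. The point supports a low-cost improvement to the plan, not a conclusion that the primary result would be invalid.

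**What to change.** Record the date of each adverse event and any days without mobilization that follow it. Keep the 7-day mean as planned, and pre-specify beside it a sensitivity analysis with the same model and covariates:

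1. Standardize each day's MQS against patients still event-free on that hospital day.
2. Average over the patient's days before the first event, or over all seven days if there was none.
3. Fit the section 2.14 model to this exposure and report both results. Interpret a favourable association cautiously if the pre-event analysis does not support it.

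The cost is a date field, a record of days without mobilization, and one further model fit on MQS data that a 7-day average already requires. The fields should be in place before enrolment opens in June 2026, since dates may not be recoverable afterwards.

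There are limits. Patients with a day-1 event drop out of the added analysis, and those with early events contribute fewer days. Deterioration that reduces dose without a recorded event is not addressed. No change to the clinical bed-rest rule is proposed.
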